**I. Study Summary**

**Study Title:**

Prophylactic Use of COVID-19 Convalescent Plasma in Adult Patients Early After Hematopoietic Stem Cell Transplantation: A Randomized Controlled Trial.

**Protocol Number:** CCP-COVID-19-HSCT-2023-V6.0

**Version and Date:** Version 6.0, January 7, 2023

**Study Phase:** Investigator-initiated clinical study (non-commercial, single-center, randomized controlled trial).

**Sponsor Institution:** Department of Hematopoietic Stem Cell Transplantation, Tianjin Institute of Hematology, CAMS & PUMC.

**Principal Investigator:** [name], Deputy Chief Physician.

**Study Objective:**

To evaluate whether prophylactic infusion of high-titer COVID-19 convalescent plasma (CCP) can reduce the incidence of COVID-19 infection during the early post-transplant period in adult HSCT recipients, compared with standard supportive care alone.

**Study Population:**

Adult patients (aged ≥18 years) within 100 days after allogeneic HSCT, without active SARS-CoV-2 infection at enrollment.

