**Primary Endpoint:**

Incidence of laboratory-confirmed COVID-19 infection within one year after HSCT.

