**Figure 1. Study schedule.**

**Timeline of convalescent plasma (CCP) infusions and virological/immunological monitoring after HSCT. CCP infusions were given on days +14, +28, +60, and +90. Twice-weekly nucleic acid and weekly antibody testing continued through day +120.**

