2.2 Rationale for Convalescent Plasma Therapy

COVID-19 convalescent plasma (CCP) contains high-titer polyclonal antibodies derived from individuals who have recovered from SARS-CoV-2 infection. These antibodies can provide passive immunity by neutralizing circulating virions, blocking viral entry into host cells, facilitating antibody-dependent cellular cytotoxicity (ADCC), and modulating inflammatory cytokine cascades.

Several studies have shown that CCP therapy is most effective when administered early in the disease course or to individuals lacking endogenous antibodies, such as immunocompromised patients and those with impaired humoral immunity.

In HSCT recipients, especially during the first 100 days post-transplant, endogenous antibody production is minimal due to delayed B-cell recovery and ongoing immunosuppressive therapy. This period corresponds to the highest incidence of viral infections and infectious mortality. The rationale for using CCP in this population is to bridge the “immune gap” between transplantation and vaccine-induced or natural antibody generation, thereby reducing early post-transplant infection risk.

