3.3 Primary Endpoint

Incidence of laboratory-confirmed SARS-CoV-2 infection within 12 months after HSCT.

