3.4 Secondary Endpoints

1. COVID-19 severity grading according to WHO Clinical Progression Scale (scores 1–10).

2. Overall survival rate at 12 months post-transplant.

3. Time to first COVID-19 diagnosis (days from transplantation to first positive test).

4. Quantitative or semiquantitative SARS-CoV-2 antibody titers measured at predefined intervals (baseline, pre-infusion, and 14, 28, 60, 90, 180, and 365 days post-transplant).

5. Number and proportion of adverse events (AEs) and serious adverse events (SAEs) related to plasma infusion, graded according to CTCAE v5.0.

6. Association between CCP antibody titer and risk reduction for COVID-19 infection or severe disease.

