4.2 Randomization and Allocation Concealment

Randomization is performed using a computer-generated sequence prepared by an independent statistician who is not involved in patient care.

Allocation follows a simple randomization design with a 1:1 ratio between the CCP group and the control group. The randomization sequence is stored securely by the data manager and concealed until the time of patient enrollment.

Upon confirmation of eligibility and signed informed consent, the investigator obtains the next available randomization code from the sealed allocation list. This process ensures that treatment assignment remains concealed until enrollment is finalized.

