4.7 Follow-Up and Assessments

| **Time Point** | **Clinical Assessments** | **Laboratory Assessments** |
| --- | --- | --- |
| Baseline (pre-transplant) | Demographics, medical history, HSCT details, donor type | SARS-CoV-2 antibody titer, PCR test |
| Day +14 | Vital signs, infusion tolerance | Antibody titer, CBC, liver/renal function |
| Day +28 | AE assessment, infection monitoring | Antibody titer, PCR test |
| 2 months | Clinical evaluation, GVHD status | Antibody titer, PCR test |
| 3 months | Clinical evaluation | Antibody titer, PCR test |
| 6 months | Infection and survival status | Antibody titer |
| 12 months | Final follow-up | Antibody titer, survival status |

COVID-19 infection is defined as PCR-confirmed SARS-CoV-2 positivity by nasopharyngeal swab or other approved method.

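### Enrolment is allowed to day 100 after HSCT, but the infusion windows start closing on day 16 and the endpoints count from HSCT, so late entry dilutes the comparison

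*Protocol*

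**What the plan says.** **Entry.** The Study Population statement in the Study Summary takes adults "within 100 days after allogeneic HSCT, without active SARS-CoV-2 infection at enrollment". Section 4.2 sets randomisation at enrolment: "Upon confirmation of eligibility and signed informed consent, the investigator obtains the next available randomization code from the sealed allocation list". Neither place sets an earlier transplant-day limit.

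**Treatment.** Section 4.4.1 schedules infusions at day +14 ± 2, day +28 ± 2, about 2 months ± 7 days and about 3 months ± 7 days. The Figure 1 legend gives the nominal days: "CCP infusions were given on days +14, +28, +60, and +90". No shifted or catch-up schedule is described for a patient who enters after a window has closed.

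**Endpoints.** Section 3.3 defines the primary endpoint as "Incidence of laboratory-confirmed SARS-CoV-2 infection within 12 months after HSCT", and the Study Summary words it the same way. Section 3.4 measures time to first diagnosis in days from transplantation.

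**Per-protocol set.** Section 5.2 requires completion of all planned study procedures in both arms and, in the CCP arm, at least four infusions.

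**Signs of earlier entry.** The assessment table in Section 4.7 places baseline before transplant, and Section 6.2 requires consent before any study procedure.

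**The concern.** Eligibility, infusion schedule and endpoint origin are all fixed in the Protocol, and they do not fit together. A patient who is eligible on day 40 can be randomised to a four-dose regimen of which only two doses remain available in window. That patient's endpoint clock has already run for 40 days, during which neither arm was treated.

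Two kinds of dilution follow. Some CCP patients are under-dosed by design. Some counted events may precede randomisation. Section 2.2 says of the first 100 days: "This period corresponds to the highest incidence of viral infections and infectious mortality". If that holds for SARS-CoV-2, the untreated days are those in which infection is most likely. A trial of 72 patients planned at 80% power has little room for either loss.

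**Working it through.** **1. Doses still available by day of randomisation.** The closing day of each window is the nominal day plus its tolerance: 14 + 2 = 16, 28 + 2 = 30, 60 + 7 = 67, 90 + 7 = 97. Months of 30.4 days would move the last two to about 67.8 and 98.2.

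| Day randomised | In-window doses possible |
|---|---|
| 16 or earlier | 4 |
| 17–30 | 3 |
| 31–67 | 2 |
| 68–97 | 1 |
| 98–100 | 0 |

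If entry were uniform over days 0 to 100 (an assumption), 17% could receive four doses, 14% three, 37% two, 30% one and 3% none. The mean is 2.1.

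**2. The plan's own sample size.** Section 5.1 gives 80% versus 50% infected at one year, two-sided α of 0.05, 80% power, a log-rank test and 72 patients. The hazard ratio is ln(0.5)/ln(0.2) = 0.693/1.609 = 0.431. Schoenfeld's formula needs 45 events, and 45/0.65 gives 70 patients before attrition. That is close to 72, although adding the stated 10% attrition would give 78. The attrition gap is a separate matter. The steps below use 72 patients without attrition.

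**3. Chance of infection before entry.** With a constant control hazard of 1.609/365 per day, the chance by day E is 1 − exp(−1.609·E/365): 6.0% by day 14, 6.8% by day 16, 12.4% by day 30 and 35.7% by day 100.

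**4. Power if only infections after entry count, full effect kept.** The expected events are d = 36·[(1 − exp(−1.609·(365−E)/365)) + (1 − exp(−0.693·(365−E)/365))], and power = Φ(√(d/4)·|ln 0.431| − 1.96).

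| Entry | d | Power |
|---|---|---|
| Day 14 | 45.9 | 0.81 |
| Uniform 0–100 | 43.1 | 0.79 |
| All at day 100 | 39.0 | 0.75 |

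**5. Power if resolved earlier infections count as worded, full effect kept.** Assume that anyone infected at least r days before entry has recovered and is enrolled. The share of enrolled patients with an earlier event is p/(p+q), with p = 1 − exp(−1.609·(E−r)/365) (zero when E is below r) and q = exp(−1.609·E/365). Power comes from a simulated log-rank test timed from HSCT, with the control hazard in both arms before entry and the hazard ratio of 0.431 after it.

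| Entry | r = 14: share, power | r = 28: share, power |
|---|---|---|
| Day 14 | 0%, 0.81 | 0%, 0.81 |
| Uniform 0–30 | 2%, 0.79 | 0%, 0.81 |
| Uniform 0–60 | 8%, 0.71 | 4%, about 0.75 |
| Uniform 0–100 | 15%, 0.61 | 11%, about 0.65 |

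For uniform 0–100 with r = 14, the one-year contrast shrinks to about 79% versus 53%. With r = 60 the share is 4% and power about 0.73. With r = 14 but only a quarter of recovered patients enrolling, power is also about 0.73. Uniform entry over days 0 to 16 gives about 0.81, which is no loss.

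Steps 4 and 5 keep the full plasma effect for every CCP patient. Missed doses would lower power further, but the Protocol gives no dose-response from which to size that.

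**The case against.** The best counter-argument is that early entry was plainly meant. The population statement is a one-line summary. The design gives every CCP patient four infusions from day +14, Section 2.3 ties the first dose to the end of isolation or discharge, and the baseline visit is before transplant. On that reading the loss is nil. This stands as evidence of intent, but none of these places caps entry, and a pre-transplant baseline sits awkwardly with a population defined as already past HSCT.

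The larger power losses need late entry, recovery within weeks and enrolment of recovered patients into a prophylaxis trial. Section 2.1 describes prolonged viral shedding, severe disease and death in this population, which argues against quick recovery with full enrolment. This also stands, and it is why the result is a range.

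The Protocol does not expressly say that pre-randomisation infections count. It follows from the HSCT origin and the absence of any exclusion, and an analysis plan could handle those events differently. The HSCT origin itself, however, is fixed in the Protocol.

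A reader might infer that the per-protocol set loses late entrants from the CCP arm only. Section 5.2 does not support that. Both arms must complete all planned procedures, so a control who entered on day 50, having missed the day +14 and day +28 assessments, could fail too. The four-infusion rule also does not itself say that doses must be in window.

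**Conclusion.** The conflict is real as written: entry is open to day 100, four in-window doses are possible only to day 16, and the endpoint wording takes in infections that plasma could not have prevented.

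A reader might infer bias in the ITT comparison. The documents do not support that, because time before randomisation is balanced between arms in expectation. The harm is dilution toward no difference, plus a per-protocol set that loses late entrants: certainly in the CCP arm if doses must be in window, possibly in the control arm as well.

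The size depends on how many patients enter late, which the Protocol does not say. It is negligible if all enter by day 16. For uniform entry over days 0 to 100, under constant hazards, no attrition and full effect, power goes from about 0.81 to about 0.79 if only post-entry infections count, and to about 0.6 to 0.75 if resolved earlier ones count. These are illustrations, not bounds. The point should be fixed because the text permits the problem and the correction is small.

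**What to change.** - **Study Population statement:** require randomisation before the first infusion and no later than day +16 after HSCT, with a negative PCR at enrolment. The day +14 row in Section 4.7 lists no PCR, but the twice-weekly nucleic acid testing in the Figure 1 legend may supply it.
- **Primary Endpoint in the Study Summary and Sections 3.1 to 3.4:** count only first infections after randomisation. Measure time from randomisation, or keep the HSCT scale with delayed entry at randomisation. All five places need the change so that objectives and endpoints agree.
- **Follow-up:** this can still end 12 months after HSCT. Entry by day 16 leaves at least 365 − 16 = 349 days at risk.
- **Baseline row in Section 4.7:** keep it as pre-transplant if consent is taken before transplant.

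The cost is one eligibility sentence, matching phrases in the objectives and endpoints, and a narrower recruitment window at a single centre.

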**Study Design:**

A prospective, single-center, open-label, randomized controlled trial.

Eligible participants are randomized 1:1 to receive either:

1. CCP group: Four planned infusions of high-titer CCP (200 mL each) at day +14, +28, ~2 months, and ~3 months post-transplant.
2. Control group: Standard supportive care without CCP.

All participants are followed for one year after transplantation.

**Primary Endpoint:**

Incidence of laboratory-confirmed COVID-19 infection within one year after HSCT.

**Secondary Endpoints:**

1. Incidence and severity of COVID-19 (mild/moderate/severe).
2. Overall survival (OS) at one year.
3. Time to first SARS-CoV-2 infection.
4. Incidence of adverse events related to plasma infusion.
5. SARS-CoV-2 antibody titers and their kinetics over time.

**Sample Size:**

72 participants (36 per group), calculated assuming infection rates of 80% in the control group and 50% in the CCP group, α = 0.05, β = 0.20, using a log-rank test.

**Study Duration:**

Total study period: 12 months after last enrollment.

Each participant: 12 months of post-transplant follow-up.

**Statistical Analysis:**

Both intention-to-treat (ITT) and per-protocol (PP) analyses will be performed. Kaplan–Meier survival curves will be generated, and group comparisons will use the log-rank test. Continuous variables will be compared using the t-test or Mann–Whitney U test; categorical variables using χ² or Fisher’s exact test.

**Safety Monitoring:**

Adverse events (AEs) and serious AEs (SAEs) will be graded according to CTCAE v5.0, summarized by severity, relationship to study treatment, and reported to the institutional ethics board.

**Ethical Considerations:**

The study is conducted in accordance with the Declaration of Helsinki (2013), GCP (ICH E6 R2), and Chinese regulatory guidelines. Written informed consent is obtained from all participants.

[figure not shown]

**Figure 1. Study schedule.**

**Timeline of convalescent plasma (CCP) infusions and virological/immunological monitoring after HSCT. CCP infusions were given on days +14, +28, +60, and +90. Twice-weekly nucleic acid and weekly antibody testing continued through day +120.**

**Ⅱ. Background and Rationale**

2.1 Background

Since its emergence in late 2019, coronavirus disease 2019 (COVID-19), caused by severe acute respiratory syndrome coronavirus 2 (SARS-CoV-2), has led to an unprecedented global pandemic. Despite the widespread implementation of vaccination programs, breakthrough infections and the emergence of new viral variants continue to pose serious threats to immunocompromised populations, particularly hematopoietic stem-cell transplantation (HSCT) recipients.

HSCT recipients represent one of the most vulnerable groups to COVID-19 due to profound and prolonged immune deficiency. Multiple studies have demonstrated that, in the early post-transplant period, patients experience severe lymphopenia, delayed T- and B-cell recovery, and diminished humoral and cellular responses to vaccination. Consequently, they remain at exceptionally high risk for prolonged viral shedding, severe infection, and death. The European Society for Blood and Marrow Transplantation (EBMT) and the American Society for Transplantation and Cellular Therapy (ASTCT) have both identified COVID-19 as a major post-transplant complication requiring preventive strategies beyond vaccination alone.

2.2 Rationale for Convalescent Plasma Therapy

COVID-19 convalescent plasma (CCP) contains high-titer polyclonal antibodies derived from individuals who have recovered from SARS-CoV-2 infection. These antibodies can provide passive immunity by neutralizing circulating virions, blocking viral entry into host cells, facilitating antibody-dependent cellular cytotoxicity (ADCC), and modulating inflammatory cytokine cascades.

Several studies have shown that CCP therapy is most effective when administered early in the disease course or to individuals lacking endogenous antibodies, such as immunocompromised patients and those with impaired humoral immunity.

In HSCT recipients, especially during the first 100 days post-transplant, endogenous antibody production is minimal due to delayed B-cell recovery and ongoing immunosuppressive therapy. This period corresponds to the highest incidence of viral infections and infectious mortality. The rationale for using CCP in this population is to bridge the “immune gap” between transplantation and vaccine-induced or natural antibody generation, thereby reducing early post-transplant infection risk.

2.3 Scientific Basis for Timing and Dosing

The CCP infusion schedule in this study—at day +14, day +28, approximately 2 months, and 3 months post-transplant—was designed to align with both immunologic recovery kinetics and clinical milestones in HSCT care:

1. Day +14: Represents the period of deepest lymphopenia and hypogammaglobulinemia, coinciding with protective-isolation discontinuation or discharge following engraftment. Passive antibody transfer at this stage provides coverage when vaccine response is absent.
2. Day +28: The half-life of IgG (~21 days) suggests waning antibody levels after the first infusion; a second dose extends protection during ongoing immune insufficiency.
3. ~2 months: Around day +60 marks the immunologic “transition point,” when partial lymphocyte recovery occurs but humoral immunity remains immature.
4. ~3 months: Vaccine immunogenicity remains poor within 3–6 months post-HSCT; this dose bridges the gap until active immunity can be established.

This “bridge-immunity” strategy integrates pathophysiological and clinical-pathway considerations to maintain continuous protection throughout the most vulnerable early post-transplant phase.

2.4 Study Significance

Despite extensive clinical experience with convalescent plasma in severe or critical COVID-19 cases, data on its prophylactic use—particularly among HSCT recipients—remain extremely limited. Given the delayed immune reconstitution and poor vaccine responses in this population, early passive immunization represents a rational, low-toxicity approach to reduce infection risk and mortality.

This trial aims to provide high-quality prospective evidence regarding the feasibility, safety, and efficacy of prophylactic CCP administration in adult HSCT recipients, filling an important knowledge gap in post-transplant infectious prophylaxis.

**Ⅲ. Study Objectives and Endpoints**

3.1 Primary Objective

To evaluate whether prophylactic infusion of high-titer COVID-19 convalescent plasma (CCP) reduces the incidence of laboratory-confirmed SARS-CoV-2 infection within one year after allogeneic hematopoietic stem-cell transplantation (HSCT), compared with standard supportive care alone.

3.2 Secondary Objectives

1. To assess the severity and clinical course of COVID-19 infection (mild, moderate, severe, or critical) in CCP versus control groups.

2. To evaluate overall survival (OS) at one year post-transplant.

3. To determine the time to first SARS-CoV-2 infection after transplantation.

4. To assess the kinetics and durability of anti–SARS-CoV-2 antibody levels following CCP infusion.

5. To evaluate the safety and tolerability of CCP administration by recording infusion-related and systemic adverse events.

6. To explore correlations between antibody titers and clinical outcomes.

3.3 Primary Endpoint

Incidence of laboratory-confirmed SARS-CoV-2 infection within 12 months after HSCT.

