**Ⅴ. Statistical Considerations**

5.1 Sample Size Determination

The sample size was calculated based on the expected difference in the incidence of COVID-19 infection between the CCP group and the control group.

According to preliminary clinical observations and published data, the infection rate within one year after HSCT was estimated at 80% in the control group and 50% in the CCP group.

Assuming a two-sided significance level (α = 0.05) and a statistical power of (1 – β = 0.80), and using a log-rank test for comparison between groups, the required total sample size was calculated to be 72 participants (36 per group).

This number also accounts for an estimated 10% attrition rate due to loss to follow-up or early withdrawal.

The sample-size calculation was performed using PASS software version 15.0 (NCSS, Kaysville, UT, USA).

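### The primary endpoint runs to 12 months on a PCR definition, but the two PCR schedules differ, both stop by day +120, and no common testing rule covers the remaining months of an open-label trial

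*Protocol*

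**What the plan says.** Section 3.3 sets the primary endpoint as "Incidence of laboratory-confirmed SARS-CoV-2 infection within 12 months after HSCT". Section 4.7 gives the case definition: "COVID-19 infection is defined as PCR-confirmed SARS-CoV-2 positivity by nasopharyngeal swab or other approved method".

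The protocol describes the PCR schedule in two places:

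- **Section 4.7 table.** PCR is listed at baseline, day +28, 2 months and 3 months. The last row with a PCR is "3 months | Clinical evaluation | Antibody titer, PCR test". The later rows are "6 months | Infection and survival status | Antibody titer" and "12 months | Final follow-up | Antibody titer, survival status". Neither contains a PCR.
- **Figure 1 legend.** "Twice-weekly nucleic acid and weekly antibody testing continued through day +120".

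Section 4.1 says participants are followed for infection status throughout the 12 months. Section 4.3 makes the trial open-label for investigators and participants, and blinds the laboratory staff who run the SARS-CoV-2 and antibody tests. No passage states what prompts a PCR outside the scheduled tests.

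Section 5.1 plans 36 patients per arm on the basis that "the infection rate within one year after HSCT was estimated at 80% in the control group and 50% in the CCP group".

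**The concern.** The endpoint can be met only by a positive PCR, yet planned PCR covers at most the first third of the window (120 of 365 days). The count therefore mixes two kinds of ascertainment: scheduled testing early, and testing for unspecified reasons later.

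In the later period a mild or asymptomatic infection counts only if someone has the patient tested. The people who make that decision know the arm. A control patient who feels exposed, or a clinician who believes the plasma patient is protected, may act differently. Laboratory blinding protects how a swab is read, not whether it is taken.

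The antibody titers at 6 and 12 months do not fill the gap. They are outside the case definition, and one arm has been infused with antibody.

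The two schedules also imply very different detection in the early period: three post-transplant PCRs in the table, against twice-weekly testing in the figure. An analysis plan cannot repair this afterwards, because infections that were never tested for cannot be recovered.

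**Working it through.** **Inputs.** One-year infection of 80% (control) and 50% (CCP), 36 per arm, log-rank test, two-sided α 0.05, power 0.80 and 10% attrition, all from section 5.1. Last scheduled PCR at 3 months (taken as day 90) from the section 4.7 table, or day 120 from the Figure 1 legend. The protocol gives no infection-time distribution, so the hazard shape is an assumption and is varied below.

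**Step 1: reproduce the plan's sample size.** HR = ln(0.5)/ln(0.2) = 0.431. A Lakatos-type log-rank calculation with constant hazards, 12-month follow-up and 10% loss over the year gives N = 72.06, which matches the stated 72. Without loss it gives 69. The constant-hazard model is therefore consistent with the plan's own figure, although the protocol does not state it.

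**Step 2: planned events.** 36 × (0.80 + 0.50) = 46.8.

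**Step 3: share after the last scheduled PCR, constant hazard, no loss.** Infected by day t = 1 − (1 − p)^(t/365).

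- Day 120: control 1 − 0.2^(120/365) = 41.1%; CCP 1 − 0.5^(120/365) = 20.4%. Late share = 1 − (0.411 + 0.204)/1.30 = 52.7%, or 24.7 events. By arm it is 48.6% of control events and 59.2% of CCP events.
- Day 90: control 32.8%, CCP 15.7%. Late share = 1 − (0.328 + 0.157)/1.30 = 62.7%, or 29.4 events.

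**Step 4: higher early hazard.** Let the hazard before day 100 be m times the later hazard, with the one-year rates held fixed. The fraction of the one-year cumulative hazard used by day 120 is (100m + 20)/(100m + 265), and by day 90 it is 90m/(100m + 265). That fraction replaces t/365 in Step 3.

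| Early-to-late hazard ratio m | Late share, cut at day 120 | Late share, cut at day 90 |
|---|---|---|
| 1 (constant) | 53% | 63% |
| 1.5 | 44% | 53% |
| 2 | 37% | 46% |

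The share falls to one half at m = 1.13 (day 120) or m = 1.7 (day 90).

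**Step 5: illustration of bias with no true effect.** Take 80% one-year infection in both arms, full detection to day 120 and constant hazards. True late incidence is 0.80 − 0.411 = 0.389. The detection rates are assumptions.

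- 80% versus 60% detected late: 0.20 × 0.389 = 7.8 points.
- 80% versus 70% detected late: 0.10 × 0.389 = 3.9 points.
- With m = 2, true late incidence is 0.80 − 0.533 = 0.267, and 80% versus 60% gives 5.3 points.

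**Step 6: cost of shortening the primary window.** To day 120 under constant hazards, expected events are 36 × (0.411 + 0.204) = 22.1. Schoenfeld power at the same HR is Φ(√22.1/2 × |ln 0.431| − 1.96) = Φ(1.98 − 1.96), or about 51%. To day 90 it is about 17 events and 42%.

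**The case against.** Four points on the other side have weight.

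- **How many events are late.** A reader might infer that over half of the primary events rest on unscheduled testing. The documents do not establish that. It needs a constant hazard, and with the day +120 schedule it is marginal: 52.7%, and under half in the control arm. Section 2.2 describes the first 100 days as the period of highest viral infection incidence, which points to a lower late share. A range is all that can be claimed.
- **What is unblinded.** A reader might also call the late testing unblinded. Section 4.3 blinds the testing laboratory. Only the decision to seek or order a test is open.
- **Follow-up continues.** Section 4.1 and the 6-month row of the table provide for infection status after day +120, so the period is not unobserved. What is missing is a planned PCR or a common rule for obtaining one.
- **The schedules might be layered.** The table could list visit tests while the figure describes separate surveillance. The protocol does not say so, and the legend gives no start day. The two passages still need to be reconciled.

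The bias figures show what is possible, not what is likely. The documents support no particular detection rates and no direction by arm. The 7.8 and 3.9 points compare with a planned difference of 30.

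None of this removes the core point. The endpoint outlasts scheduled PCR by about eight to nine months, and testing in that time is left to people who know the arm.

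**Conclusion.** The point holds as a defect in how the primary endpoint is ascertained. Two things follow from the text alone: the two PCR descriptions differ, and neither reaches beyond day +120 of a 12-month PCR-defined endpoint.

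The size depends on infection timing, which the protocol does not give. Roughly 37% to 63% of planned events fall after the last scheduled PCR over the scenarios examined, and the upper part of that range (53% to 63%) requires constant hazards. Even the lowest figure is more than a third of the primary events. A spurious difference of about 4 to 8 points is an illustration under assumed detection rates and constant hazards. It is not evidence that the arms would be tested differently.

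**What to change.** 1. Reconcile the section 4.7 table and the Figure 1 legend into one PCR schedule, identical in both arms.
2. Keep 12 months as the primary window, and state one PCR trigger rule applied identically in both arms through month 12.
3. Report infections up to and after the end of scheduled testing separately, split into scheduled and triggered detections.
4. Prespecify infection to day +120 as a sensitivity or secondary analysis, once the reconciled schedule confirms that testing to that day is the same in both arms. It should become primary only if the power is restated, given the roughly 51% at N = 72 shown above.
5. Swabs at the existing 6- and 12-month visits are optional. They would detect only infection present on those days, so they cannot replace the trigger rule.

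The cost is a protocol amendment, some additional triggered tests and a little more analysis.
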